### Recruitment and randomization (see Fig. 1)

This will be a pioneer study in populations with SMI and, for this reason, reference figures from similar studies [31] have been used to calculate the sample size, adjusted to the characteristics and severity of the sample. Abstinence after 12 months was estimated at 3 and 15% in the control and experimental branches, respectively. A level of confidence of 95% and a power of 80% is assumed, which requires a minimum of 85 patients per branch, with an added 20% for possible losses during follow-up.

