**Fig. 1 Fig1:**
[figure not shown]
Flow diagram of study design

Recruitment of at least 204 patients who meet all the inclusion criteria and none of exclusion criteria will be carried out over 1 year and follow-up appointments will be arranged after that.

Inclusion criteria: (1) patients aged between 40 and 70 years; (2) confirmed diagnosis of BD or Schizophrenia according to *Diagnostic and Statistical Manual of Mental Disorders, 4th edition, text revision* (DSM-IV-TR); (3) active smokers who currently consume at least 10 CPD, with a cumulative consumption of 10 packets/year or more; (4) have signed an informed consent to participate in the study.

Exclusion criteria: (1) previous respiratory diagnosis of: asthma, cystic fibrosis, tuberculosis, simple chronic bronchitis, restrictive pulmonary disease or bronchiectasis; (2) acute respiratory symptoms; (3) heart disease or advanced oncological processes; (4) existence of a pathology which makes it advisable not to perform spirometry (recent pneumothorax, recent thoracic or abdominal surgery, aortic aneurysm, unstable angulation, retinal detachment, facial hemiparesis or oral/dental problems); (5) patients who, due to their intellectual disability or mental pathology, do not understand or cannot be forced to perform spirometry; (6) clinical instability with results of over 14 points on the Hamilton Depression Rating Scale (HDRS), a Young Mania Rating Scale (YMRS) score of over 6 or a Positive and Negative Syndrome Scale (PANSS) score of over 70.

The randomization will be carried out using the *Redcap* [32] program, as implemented by the Bioinformatics Unit of IMIBIC (the Maimónides Institute of Biomedical Research in Córdoba, Spain). It will be centralized, performed in permuted blocks and stratified by center, age, gender and pathology. The ratio will be 1:1 for each arm. The research staff will have no knowledge of the assignment until the patient signs their informed consent and has been included in the system (which will automatically assign the patient, once included, to a particular arm).

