### Statistical analysis

The statistical analysis will include all the patients randomized to both branches according to an intention-to-treat approach. The main variable for smoking cessation will be analyzed using the chi-square test for qualitative variables, which in this case consist of the differences between the control and intervention groups. The effect size will be expressed as relative risk (RR), absolute risk reduction (ARR) and the number needed to treat (NNT), with the corresponding 95% confidence interval (CI). The secondary variables will require the comparison of the average values of the quantitative variables between groups (level of motivation, consumption of tobacco according to CPD and expired CO) and will be carried out using Student’s *T* test and its respective post-hoc correction tests. The Mann-Whitney *U* test will be used for the non-parametric equivalent. The association between the quantitative variables will be evaluated using bivariate correlation tests, such as Pearson’s linear correlation coefficients (parametric test) or Spearman’s correlation coefficients (non-parametric test). The respiratory variables for the presence of COPD and its staging will require a descriptive analysis and the results will be presented as frequencies and percentages. Logistic regression models will be used for the multivariate analysis. To control any effects in the comparison between groups caused by contact with the addiction treatment network or the neurocognitive evaluation, the variables associated with these events will be collected and the corresponding adjustments made in the analysis.

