Nonetheless, considering their obvious limitations, the results should be analyzed carefully. Despite the open design of this study, due to the characteristics of the intervention under evaluation, the main variables of efficacy and damage can be measured objectively through the techniques of cooximetry and spirometry. The intensity of the experimental intervention can be measured by two factors: the motivational value of the individualized information and the importance of keeping up motivation in the future. The control intervention is less intense, although much greater than the usual option offered in this type of population. The intervention is not designed to propose any specific treatment, but to prepare the patient for starting treatment and for attending, when ready, the specialized Addictions Network. Once in the real world the type of treatment, level of adherence and results will all be assessed objectively.

Community mental health care constitutes the ideal setting for developing an intervention model based on prevention. A multidisciplinary team who are familiar with SMI patients and their health needs can offer them, through regular follow-up checks, a new way of approaching the problem of smoking through early diagnosis and motivation. Studying the lung function using spirometry is a valid way of doing this, as long as the health professionals are suitably trained, and the results are accurately validated and interpreted by a specialist.

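### The plan adjusts the between-arm comparison for addiction-network contact, a post-randomisation step that the intervention is meant to bring about, so the adjusted result no longer estimates the total effect

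*Protocol article*

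**What the plan says.** Three parts of the protocol article bear on this.

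- **Statistical analysis.** Cessation is compared between all randomised patients by an unadjusted chi-square test, with relative risk, absolute risk reduction and number needed to treat. The section then says "Logistic regression models will be used for the multivariate analysis". It closes by naming two possible influences on the group comparison, use of the addiction network and the neurocognitive evaluation, and promises that "the variables associated with these events will be collected and the corresponding adjustments made in the analysis".
- **Discussion.** The intervention does not itself deliver a treatment. It is meant "to prepare the patient for starting treatment and for attending, when ready, the specialized Addictions Network".
- **Recruitment and randomization.** "Abstinence after 12 months was estimated at 3 and 15% in the control and experimental branches, respectively". At least 204 patients are to be recruited, and "The ratio will be 1:1 for each arm".

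The Data collection and monitoring section lists the network variables (referral request, number of appointments, treatment offered) and three neurocognitive measures (Digit Span backwards, Trail Making A and B). It says the neurocognitive tests are also there to detect change following the intervention.

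**The concern.** Whether a patient reaches the addiction network is decided after allocation and is the route by which the motivational intervention is supposed to lead to quitting. Treating it as a nuisance to be controlled conditions on part of the treatment's own effect. The adjusted odds ratio would then answer a narrower question than the stated objective, which is whether the intervention helps patients quit.

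It would not be a clean direct effect either. Patients who seek the network are likely to differ in motivation from those who do not, and randomisation does not balance that difference within levels of contact.

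The neurocognitive scores raise the same issue if follow-up rather than baseline values are used. The event count adds a second, smaller problem: few quitters are expected, so a model with several terms will be imprecise.

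**Working it through.** **Planned size.** Inputs: 3% v 15%, "A level of confidence of 95% and a power of 80% is assumed" (two-sided 5% assumed, since sidedness is not stated). With unpooled variance:

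n = (1.960 + 0.842)² × (0.03×0.97 + 0.15×0.85) / 0.12² = 7.85 × 0.1566 / 0.0144 ≈ 85.4 per arm.

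This agrees with the stated 85. Then 85 × 1.2 = 102 per arm and 204 in total, as planned.

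**Expected quitters.**
- 102 per arm: 102×0.03 + 102×0.15 = 3.06 + 15.30 = 18.4.
- 85 per arm: 2.55 + 12.75 = 15.3.
- Chance of no control quitter: 0.97^102 = 4.5%; 0.97^85 = 7.5%.

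**Events per parameter, using only the terms the plan names.** Arm + one network term + three neurocognitive scores = 5 parameters: 18.4/5 = 3.7 (15.3/5 = 3.1 at 85 per arm). If all three network variables enter as one term each, there are 7 parameters and 18.4/7 = 2.6.

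**Sparse-data bias from those terms.** True OR = (0.15/0.85)/(0.03/0.97) = 5.71. These are simulated trials at 102 per arm with covariates that have no effect; maximum-likelihood results are summarised where the treatment estimate was finite.
- Paired comparison (3,000 trials): geometric-mean OR 6.24 with arm only and 6.47 with the stated terms, a difference of 0.037 in log OR. exp(0.037) = 1.04, so about 4% extra.
- Separate runs (1,500 trials per model): 6.2 and 6.5, with 95% interval coverage of 96.6% and 97.5%.
- Firth fit with the stated terms: mean log OR 1.733, so OR exp(1.733) = 5.7, with coverage 96.1%.

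**Effect of adjusting for network contact.** The documents give no contact rates, so these are assumptions. Let c be the contact rate in an arm and m the log odds ratio of quitting with contact. Choose the intercept a in each arm so that the arm's overall quit rate is as planned:

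c × expit(a + m) + (1 − c) × expit(a) = 0.03 (control) or 0.15 (experimental).

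The OR conditional on contact is exp(a_exp − a_control). Simulated values are geometric means from 3,000 trials, with three null neurocognitive scores also in the adjusted model.

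| Contact, control v experimental | Contact OR | Conditional OR by formula | Simulated unadjusted OR | Simulated adjusted OR | Change in log OR |
|---|---|---|---|---|---|
| 30% v 30% | 1 | 5.71 | 6.24 | 6.47 | +0.04 |
| 20% v 40% | 4 | 4.38 | 6.14 | 4.88 | −0.23 |
| 15% v 50% | 6 | 3.01 | 6.05 | 3.22 | −0.63 |

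All three rows have the same total effect, 3% v 15%. In the second and third rows adjustment lowers the OR by 1 − exp(−0.23) = 21% and 1 − exp(−0.63) = 47%. When contact is equal between arms and unrelated to quitting, nothing is lost.

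**The case against.** The strongest reply is that the primary conclusion does not rest on this model. Cessation is tested by an unadjusted chi-square in all randomised patients, and no odds ratio is named as an effect measure. The article gives no estimator, outcome or covariate list for the logistic models, and such detail is commonly left to the full protocol or analysis plan, which are not shown. All of this stands. It makes the point one about a supportive analysis and rules out any criticism of missing detail.

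It does not dispose of the network term. Adjusting the group comparison for that contact is a stated commitment, and an analysis plan that follows it inherits the problem.

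One could also say that the authors want to separate the motivational message from the treatment that follows, which both arms may seek. That is a fair question, but it is one for a mediation analysis with its own assumptions.

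A reader might infer more: that ordinary logistic regression with the stratification factors and nine centres added is planned, and that it must inflate the adjusted effect. The documents do not support this. Centre, age, gender and pathology appear only as randomisation strata, and no section puts them in a model. With the named terms alone, upward bias is about 4% and interval coverage is sound. The possibility of no control quitter is not specific to this model either, since it leaves the relative risk without a finite value too.

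**Conclusion.** The point holds as a fault in a stated supportive analysis. Adjusting for network contact means the adjusted OR no longer estimates the total effect, and it would probably be attenuated. Illustratively it falls from about 6 to 4.9 or 3.2.

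The size depends wholly on assumed contact rates and an assumed contact effect. The direction rests on contact being more frequent in the experimental arm and helping patients quit, which is what the Discussion anticipates. Because sicker or more motivated patients may select themselves into contact, the direction is likely but not certain.

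Separately, about 18 expected quitters and about 3.7 events per parameter make the adjusted OR imprecise. This assumes the planned rates hold and that each named measure enters as a single term. It is not evidence of material inflation. The primary test is untouched, so this should be corrected but does not threaten the main result.

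**What to change.** - Keep the unadjusted chi-square test, with relative risk and risk difference, as the primary analysis.
- Remove network contact from every model of the treatment effect. Report it by arm as an outcome, or use it in a separate, labelled mediation analysis.
- Limit any supportive adjusted logistic model to arm plus a few baseline covariates named in advance. If neurocognitive scores are used, take baseline values, not follow-up values.
- Preferably fit that model with Firth's penalty, which stays finite when an arm has no quitters.

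The cost is wording only, with no change to sample size or data collection. The supportive model carries fewer covariates, and the penalised odds ratio is shrunk slightly.

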#### Experimental group

This group will go through a spirometry study for a lung age and obstruction degree determination. The anti-smoking intervention will follow the same duration and general structure of the control group. In this case, when talking about the health risks, personalized information about the lung damage and prevention opportunities will be included. It will teach the patients about comparing lung age with chronological age and explain how the formula is calculated and the origin of the damage. After evaluating their COPD, the patients will be informed about its existence and staging. Depending on the damage found, the generation of motivation will focus on different prevention methods. Likewise, after the motivation level is set, the patients will be offered the option of treatment and regular follow-up. The intervention will be strengthened by motivational messages (designed by specialists from our Addiction Network) in an attempt to give continuity to personal message based on MI—half of which are linked to the possibility of preventing respiratory damage—and sent to the patient's mobile phone via SMS during the 3 months after the face-to-face intervention, with a decreasing rate: three messages per week in the first month, and two and one per week in the following months, respectively (see Table 1 for examples of these messages) [35]. Patients without mobile phones will receive a call on their phone to convey the same messages.

**Table 1 Tab1:** Examples of text messages (SMS) sent to patients in the intervention group

Wanting to smoke is temporary, but the damage to your lungs is permanent – Which kind of suffering do you want to choose?	
The pleasure of breathing in deeply and enjoying a beautiful spring morning would be easier with cleaner lungs. How about trying it?	
Did that little run down the street leave you breathless? Ever thought about giving up smoking? Life is much more bearable with clean lungs.	
If your lungs could speak, they’d be really angry at how you are treating them. It’s up to you – you can make your life better.	
Better health and lung capacity, more cash to spend and less smelly clothes. That’s what you gain when you give up smoking. Difficult to imagine giving up? You’re not alone! Come and see us and we’ll plan it together.	

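### Adjusting the arm comparison for contact with the addiction network removes whatever part of the effect runs through that contact, and the plan does not confine the adjustment to secondary analyses

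*Protocol article*

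**What the plan says.** The Statistical analysis section of the Protocol article opens with an intention-to-treat analysis of all randomised patients. It assigns the main cessation variable to a chi-square test, with relative risk, absolute risk reduction and number needed to treat. Logistic regression is then named for multivariable work. The closing sentence addresses effects on the comparison between arms, and its operative words are "contact with the addiction treatment network or the neurocognitive evaluation, the variables associated with these events will be collected and the corresponding adjustments", to be made in the analysis. It names no outcome, no model and no time point for these variables.

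Data collection and monitoring lists the network variables: the request for referral, the number of appointments and the treatment offered. The Discussion says the intervention is designed "to prepare the patient for starting treatment and for attending, when ready, the specialized Addictions Network". In the Experimental group section, once motivation has been rated, "the patients will be offered the option of treatment and regular follow-up". The Control group section makes a similar offer, depending on how motivated the patient is.

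**The concern.** The plan treats network contact as a nuisance to be controlled when the arms are compared. Contact is not a baseline characteristic. It follows the motivational session, and by the Discussion's own account it is something the intervention tries to bring about. It therefore lies on a path from allocated arm to quitting.

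Holding it fixed has two consequences. The adjusted estimate omits the share of benefit that comes from patients being moved to seek treatment. It also compares patients who sought contact in one arm with those who sought it in the other, and these groups need no longer be alike in motivation or other causes of quitting, because randomisation balanced the arms and not these subgroups.

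At stake is the answer to the second objective at the end of the Background, the effectiveness of the intervention. If the adjusted and unadjusted results differ, the adjusted one could be presented as the corrected answer although it estimates something else.

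**Working it through.** **1. The contrast the trial was sized for.** Recruitment and randomization sets the inputs: "Abstinence after 12 months was estimated at 3 and 15% in the control and experimental branches, respectively". The other inputs there are 95% confidence and 80% power, and the stated result is 85 per arm, raised by 20% to allow for dropout. Sidedness is not stated; two-sided 5% is taken. With unpooled variance:

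n per arm = (1.960 + 0.842)² × (0.03×0.97 + 0.15×0.85) / 0.12² = 7.849 × 0.1566 / 0.0144 = 85.36.

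This agrees with the stated 85, and 85 × 1.2 × 2 = 204 agrees with the stated total. The trial is thus sized on the raw difference of 12 points. The matching odds ratio is (0.15/0.85) / (0.03/0.97) = 5.71. No covariate enters.

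**2. Order of events.** Randomisation comes first, then the motivational session, then the offer of treatment and follow-up (Control group and Experimental group sections). Network contact can only come after that. It is a consequence of arm and motivation, not a confounder of the randomised comparison.

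**3. Size of the attenuation (illustration).** The documents give no contact rates and no quit rates by contact, so these are assumptions. Controls quit at 25% with contact and 1% without. To give 3% overall, control contact must be (0.03 − 0.01) / (0.25 − 0.01) = 8.3%. Let s be the share of the 12 points that runs through contact. Then:

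- contact in the experimental arm = 8.3% + 0.12 × s / 0.24;
- direct gain in each contact stratum = 12 × (1 − s) points.

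Check at s = 0.5: contact 33.3%, quit rates 31% with contact and 7% without, so 0.333×0.31 + 0.667×0.07 = 15%, as planned.

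A logistic model with arm and contact as main effects, fitted to the exact population, gives the adjusted odds ratio and the risk difference with contact held at its pooled distribution. Rejection rates come from 1,500 simulated trials per scenario at 85 per arm, using a likelihood-ratio test of arm in that model.

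| Share through contact | Contact, experimental arm | Adjusted OR | Adjusted difference (points) | Rejection, adjusted |
|---|---|---|---|---|
| 0% | 8.3% | not computed | not computed | 86% |
| 25% | 20.8% | 4.40 | 9.5 | not run |
| 50% | 33.3% | 3.01 | 6.9 | 37% |
| 75% | 45.8% | 1.85 | 4.0 | not run |
| 100% | 58.3% | 1.00 | 0.0 | 7% |

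In the three simulated scenarios the unadjusted test rejects in about 81% of trials. The unadjusted odds ratio is 5.71 and the unadjusted difference 12 points in every row. The fall in the risk difference shows that the change is not merely a property of the odds-ratio scale.

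A second set of assumptions (102 per arm, contact 10% against 35%, direct odds ratio 2.8) gives a similar picture. Power falls from 89–91% to 35–37% across two runs, with an adjusted odds ratio of 2.9 to 3.0.

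**4. What this leaves out.** The scenarios contain no common cause of contact and quitting. The possible bias from motivation is therefore argued from structure and not quantified.

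**The case against.** The strongest reply is that the primary result is safe. The main cessation variable is assigned to a chi-square test in all randomised patients, with its own effect measures, and a chi-square test takes no covariates. The adjustment sentence comes last, just after the logistic models, and is most naturally read as an additional analysis. This largely stands: the total effect remains in the plan, and precedence between the two results is partly implied. But the sentence speaks of the comparison between groups and of the analysis in general, and does not restrict itself to secondary models.

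A reader might go further and infer that the adjustment removes the effect the trial exists to measure. The documents do not support that. The Experimental group section describes lung-age feedback, information on COPD and three months of text messages, any of which could lead to quitting without network contact. Only one of the five example messages in Table 1 invites a visit. An adjusted odds ratio of 1.0 is built into the full-mediation scenario and is not evidence about this trial.

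Contact is also open to controls, and asking how much of the effect depends on treatment received is a fair secondary question. That stands, provided the analysis is labelled as such.

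On neurocognition, the Statistical analysis section does not say that a score taken after the intervention enters any model, and the Discussion suggests a role for cognition in how patients take up the information. This limb is conditional: baseline scores are acceptable covariates, and post-intervention scores would raise the same problem.

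Finally, an article may leave modelling detail to a fuller plan. Here, however, the article states an adjustment that conflicts with its own account of the intervention; this is not an omitted detail.

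**Conclusion.** The concern holds for the adjusted comparison. It conditions on a post-randomisation variable that the intervention aims to change, so it is not the intention-to-treat effect. It removes the part acting through network contact and may add bias of unknown size and direction. The chi-square comparison is unaffected.

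Under the assumed rates the odds ratio moves from 5.7 to between 4.4 and 1.0 as the mediated share goes from 25 to 100%; at 50% the chance of detecting the arm effect drops from about 81% to 37%. The true mediated share is unknown, so these figures show a range and do not predict the result.

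**What to change.** Replace the closing sentence of the Statistical analysis section with wording that:

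- names the unadjusted intention-to-treat comparison as the answer to the effectiveness objective;
- keeps network contact out of any model that estimates the treatment effect, and admits baseline covariates only, including baseline but not post-intervention neurocognitive scores;
- reports referral requests, appointments and treatment received by arm as process outcomes;
- labels any contact-adjusted or mediation analysis exploratory.

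The cost is a few lines of analysis wording, with no extra patients. The network variables are already to be collected, and the Discussion already foresees recording the type of treatment. The change should be made before outcomes are examined by arm, so that the choice between two differing estimates does not depend on the results.
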